##### Mini-mental state examination

2.6.1.2

The MMSE was developed by Folstein et al. (34) as a cognitive screening tool. It consists of 30 items covering orientation (time/place), memory, attention, calculation, language, and visuospatial abilities, with a total score of 30 points. A score of 24 or above is considered indicative of normal cognitive function, with higher scores reflecting better cognition. The MMSE is easy to administer, has clearly defined scoring criteria, and takes only 5–10 min to complete. It demonstrates good sensitivity, specificity, and reliability, making it one of the most widely used cognitive screening tools worldwide. Research has shown that MMSE scores are influenced by educational attainment (35). Therefore, education-stratified cut-off values have been recommended: ≤19 for illiterate individuals, ≤22 for those with primary education (≤6 years), and ≤26 for those with junior high school education or above.

##### Short physical performance battery

2.6.1.3

The SPPB scale will be used to assess the motor function of the study participants (36). The SPPB consists of three components: balance, gait speed, and lower limb strength, which are assessed through three tests: balance test (standing with feet in side-by-side, semi-tandem, and tandem positions), 4-meter walking speed test (measuring the time taken to walk a 4-meter distance), and the repeated chair stand test (5 repetitions of standing up from a chair). The total score ranges from 0 to 12, with higher scores indicating better physical function and lower levels of activity limitations. According to the established scoring criteria, a score of ≥10 indicates normal motor function, while a score of <10 indicates abnormal motor function.

##### Mini nutritional assessment

2.6.1.4

This study will use the MNA scale (37) to assess the nutritional status of the participants. The MNA scale consists of 4 sections and 18 questions, covering anthropometric measurements (e.g., weight, height, arm circumference), overall assessment (lifestyle, activity level), dietary evaluation (types and amounts of food, eating habits), and subjective assessment (self-rating and others’ evaluations). The assessment process is as follows: If the score for the first 6 items is >12, it indicates normal nutritional status, and no further evaluation is needed. If the score is ≤12, it suggests the risk of malnutrition, and further evaluation is required. The total score ranges from 0 to 30, with ≥24 indicating good nutrition, 17–24 suggesting risk of malnutrition, and <17 indicating malnutrition (37).

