#### Quantitative outcome measures

2.6.1

The participants in both the intervention and control groups will be assessed on their intrinsic capacity, covering six domains, including cognitive function, motor function, vitality, vision, hearing, and depression. Assessments will be conducted at T_0_, T_1_, and T_2_. For a detailed description of data collection, refer to Table 2.

**Table 2 tab2:** Overview of data collection.

Measures	T_0_	T_1_	T_2_
Demographics	△		
ICOPE screening tool	△	△	△
MMSE	△	△	△
SPPB	△	△	△
MNA	△	△	△
Visual acuity test	△	△	△
Hearing test	△	△	△
PHQ-9	△	△	△

T_0_, pre-intervention (week 0); T_1_, post-intervention (week 12); T_2_,1-month follow-up (week 16); ICOPE, Integrated Care for Older People; MMSE, Mini-Mental State Examination; SPPB, Short Physical Performance Battery; MNA, Mini Nutritional Assessment; PHQ-9, Patient Health Questionnaire-9.

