##### Patient health Questionnaire-9

2.6.1.7

The PHQ-9 (38) contains nine items, including loss of pleasure, low mood, sleep difficulties, lack of energy, eating disorders, low self-esteem, concentration difficulties, slow movement, and self-harm/suicidal ideas. These items use a 4-point Likert scale, ranging from “not at all” to “nearly every day.” The total score ranges from 0 to 7, with a higher score indicating a higher severity. This scale had a satisfactory Cronbach’s *α* coefficient among students (39) and the internal consistency of the scale was also good.

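### The MNA stops after six items when the score exceeds 12, so a 0–30 total analysed as a score would be missing for the best-nourished; the PHQ-9 range and MNA classes also need correction

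*Protocol article*

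**What the plan says.** **MNA (section 2.6.1.4).** The instrument is described thus: "The MNA scale consists of 4 sections and 18 questions". Administration has two steps. Above 12 on the first six items: "If the score for the first 6 items is >12, it indicates normal nutritional status, and no further evaluation is needed". Otherwise: "If the score is ≤12, it suggests the risk of malnutrition, and further evaluation is required". The total and its classes follow: "The total score ranges from 0 to 30, with ≥24 indicating good nutrition, 17–24 suggesting risk of malnutrition, and <17 indicating malnutrition". No rule assigns a total to a participant who stops after six items.

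**Timing and analysis.** Section 2.6.1 states "Assessments will be conducted at T_0_, T_1_, and T_2", and Table 2 lists the MNA, MMSE and PHQ-9 at all three times. Section 2.8 analyses the change in outcome indicators by group, time and their interaction in a generalized linear mixed model. It also allows t-tests, Mann–Whitney tests and χ² tests. It does not say which of these applies to the MNA.

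**PHQ-9 (section 2.6.1.7).** Nine items on a 4-point scale are described, and then: "The total score ranges from 0 to 7, with a higher score indicating a higher severity".

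**MMSE (section 2.6.1.2).** A general limit is given first: "A score of 24 or above is considered indicative of normal cognitive function". Recommended cut-offs that depend on education come next, as this list: "≤19 for illiterate individuals, ≤22 for those with primary education (≤6 years), and ≤26 for those with junior high school education or above". The section does not say which the trial will use.

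**The concern.** A stop rule is workable when an instrument is used once, to screen. Here it is applied again after randomization, to an outcome. A participant whose first-six score rises past 12 loses the total at that visit because of having improved. The intervention includes nutritional support, so if it works, more totals disappear in the intervention arm. Missingness then depends on the outcome and differs by arm. Comparing the available totals would understate a real benefit in the MNA. Questions that were not asked cannot be recovered at the analysis stage, so an analysis plan cannot repair this later.

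The other points are textual. A PHQ-9 total outside the stated range would be common. One MNA total belongs to two classes. An MMSE impairment rate, if one is reported, would depend on an unstated choice between two rules.

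**Working it through.** **1. What is collected.** Of 18 MNA questions, 18 − 6 = 12 are not asked when the first-six score exceeds 12. For those participants the 0–30 total does not exist at that visit.

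**2. Size if the total is analysed as a score.** The protocol gives no MNA mean, SD, correlation or share above 12, so all inputs here are assumptions: total mean 22 in controls, SD 4, true benefit δ = 2, both scores normal, and correlation r = 0.6 or 0.8 between the six-item score and the total. Let p be the share of controls above 12.

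- z = Φ⁻¹(1 − p) for controls; k = z − rδ/SD for the intervention arm
- share without a total in the intervention arm = 1 − Φ(k)
- mean among those with a total: 22 − SD·r·φ(z)/Φ(z) in controls, and 24 − SD·r·φ(k)/Φ(k) in the intervention arm

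Example, r = 0.8 and p = 0.5: z = 0 and k = −0.4. The share missing in the intervention arm is 0.655. The control mean is 22 − 3.2 × 0.798 = 19.45 and the intervention mean is 24 − 3.2 × 1.069 = 20.58. The difference is 1.13 instead of 2.

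| r | Missing, control | Missing, intervention | Difference observed (true 2.0) |
|---|---|---|---|
| 0.6 | 10% | 16% | 1.76 |
| 0.6 | 20% | 29% | 1.67 |
| 0.6 | 30% | 41% | 1.61 |
| 0.6 | 50% | 62% | 1.52 |
| 0.8 | 10% | 19% | 1.56 |
| 0.8 | 20% | 33% | 1.39 |
| 0.8 | 30% | 45% | 1.28 |
| 0.8 | 50% | 66% | 1.13 |

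A simulation with 400,000 per arm agrees with these values to within about 0.02.

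**3. A second set of assumptions.** First-six mean 10–12, SD 2.2; remaining items mean 11.5, SD 2; correlation 0.6; benefit of 0.5–1.5 points on the first six and 0.5–1 on the rest. By simulation, totals are missing in 13–41% of controls and 18–68% of the intervention arm. With scores capped, the observed difference is about 47–74% of the true one. Other choices for capping, and for how the two benefits are paired, widen this to about 23–83%. The direction is always toward no effect.

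**4. If the MNA is analysed by class.** Under the assumptions of step 3, early stoppers were counted as normal, as section 2.6.1.4 allows. The between-arm difference in percent normal stays within about 2 percentage points of the result from full 18-item totals.

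**5. MNA classes.** The limits ≥24 and 17–24 both contain 24. No other total falls in two classes.

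**6. PHQ-9.** Nine items coded 0–3 give 9 × 0 = 0 to 9 × 3 = 27. Coded 1–4, they give 9 to 36. A maximum of 7 would need 7/9 = 0.78 points per item, so 0–7 cannot be reproduced.

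**7. MMSE.** Comparing the two rules score by score:

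| Education | Scores where they disagree | ≥24 rule | Education rule |
|---|---|---|---|
| Illiterate | 20–23 | impaired | normal |
| Primary | 23 | impaired | normal |
| Junior high or above | 24–26 | normal | impaired |

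**The case against.** The strongest reply is that the protocol never says the MNA total will be compared as a continuous score. It gives a two-step classification, and early stoppers are classified, as normal. The neighbouring tests (SPPB, vision, hearing) also end in normal or abnormal. If the MNA is analysed by class, everyone assessed has a result, and step 4 shows little distortion. This stands, and it makes the bias conditional. It does not remove the point, because section 2.8 leaves the analysis of a score open.

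A mixed model might recover part of the loss from other visits. But missingness is set by the six-item score at the same visit, which section 2.8 does not put in the model, and a participant above 12 throughout contributes no total at all.

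A reader might infer that the primary result, or all evidence on vitality, is compromised. The documents do not support that. The primary outcome is change in intrinsic capacity, and the only total score defined for it is the 0–5 sum in section 2.6.1.1. That sum is built from the ICOPE screening items, whose nutrition question is asked of everyone at each visit.

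A reader might also infer that the MMSE section flatly contradicts itself. It can be read as a general limit refined by education. What remains is an ambiguity that matters only if scores are dichotomised; the MMSE total is unaffected. The PHQ-9 range may well be a typing slip, and nothing shows that it will alter scoring. It is still impossible as printed.

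**Conclusion.** The point holds conditionally. If the MNA total is analysed as a score, the stop rule removes it for the best-nourished, and for more of them in the arm that improves, so the MNA domain result is biased toward no effect. The direction was the same under every assumption tried. The size cannot be fixed from the protocol: the ranges in steps 2 and 3 rest on assumed distributions and on a comparison of available totals at one visit. If the MNA is analysed only by class with early stoppers as normal, the bias is small. The primary 0–5 score is untouched in either case.

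The PHQ-9 range and the double class at 24 are wrong as written, whatever the analysis. The MMSE cut-off is a minor ambiguity. These three are text corrections and carry less weight than the MNA stop rule.

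**What to change.** - **MNA administration:** give all 18 items to every participant at T0, T1 and T2, or name the six-item score, which everyone has, as the analysed MNA outcome. State whether the MNA is analysed as a score or by class. Giving all items costs a few minutes per visit for those above 12. It has to be settled before data collection.
- **MNA classes:** place 24 in one class only, for example by writing the at-risk class as 17 to <24.
- **PHQ-9:** state the item coding and the matching range (0–27 if items are coded 0–3).
- **MMSE:** if it is to be classified, name the one rule that applies; otherwise analyse the score only.

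The last three cost only an edit to the text.

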##### Visual acuity test

2.6.1.5

This study will follow the WHO-recommended visual acuity test, including both distance and near vision assessments. Distance vision measurement: The participant will be asked to remove their glasses and stand 3 meters away from the visual acuity chart. The left, right, and both eyes will be tested. If the unaided distance vision of one eye is below 4.5, it will be considered impaired. Near vision measurement: The participant will be asked to remove their glasses and stand 33 cm away from the near vision chart. The left, right, and both eyes will be tested. If the unaided near vision of one eye is below 1.0, it will be considered impaired. Comprehensive visual function assessment: If any of the distance or near vision results for the left, right, or both eyes show impairment, the participant’s vision will be considered abnormal. Otherwise, if all vision test results are normal, the participant’s vision will be considered normal.

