4. Cognitive ability	4.1 Cognitive stimulation	4.1.1 Computer-assisted cognitive system	With the help of mouse and keyboard operation, the computerized cognitive aid system (virtual supermarket training system) can complete the preset task modules of the system in order to experience virtual shopping in an immersive way, and then achieve the goal of cognitive training in multiple fields. The system covers nine task modules, each corresponding to a precise cognitive training, specifically: ‘Memory list’ to train intentional memory; ‘Map navigation’ to exercise the ability to navigate; ‘Voice broadcasting Each module precisely corresponds to a cognitive training task, as follows: ‘Memory list’ to train intentional memory; ‘Map navigation’ to improve navigation skills; ‘Voice announcement’ to enhance unintentional memory; ‘Labeling’ to strengthen verbal naming; ‘Voice cashier prompts’ to enhance verbal receptivity; ‘Payment calculation’ to train ‘Payment Calculator’ trains numeracy; “Date Code” fosters orientation; “Prize Redemption” exercises sustained attention; and “Bus Decision Making” enhances decision-making skills. By participating in these tasks, users can train their cognitive abilities in multiple domains, such as memory, language function, executive function, attention and time orientation.
	4.2 Multi-modal exercise	Refer to 1. Motor function	
5. Sensory	5.1 Hearing devices	5.1.1 Hearing aids	Hearing aids are often the most effective solution for age-related hearing loss. They amplify sound and are beneficial for most individuals. Hearing aids can be worn over or inside the ear, making them convenient to use. However, it is essential to explain to older adults that hearing aids do not cure or reverse hearing loss, but rather help improve auditory perception.
		5.1.2 Cochlear Implants	Cochlear implants are surgically placed inside the ear to convert sound into electrical impulses, which are then transmitted to the auditory nerve. A thorough evaluation is necessary to determine whether a cochlear implant is suitable. If implantation is not possible or appropriate, older adults and their families should be provided with information and training on lip reading and sign language as alternative communication methods.

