The intervention group will participate in the study for a total duration of 16 weeks, comprising a 12-week intervention phase followed by a 4-week follow-up phase. The old patients with disabilities in intervention group will take part in the “ICOPE-Based Long-Term Care Intervention Program for old patients with disabilities in Nursing Homes” (Table 1), in addition to receiving the same routine care as the control group. The intervention program was designed to enhance physical, nutritional, psychological, cognitive, and sensory functions, as well as to provide comprehensive health education and guidance. It comprised the following six components: (1) Motor function: training incorporated resistance training, aerobic exercise, flexibility training, and balance training, with each session lasting 30–45 min, twice per week. (2) Nutrition: nutritional support was tailored to individual needs based on nutritional status assessments, ensuring a balanced diet and appropriate oral supplementation. (3) Psychological function: ① Problem-solving counseling or therapy, 30–45 min per session, once every 2 weeks; ② Behavioral activation with a reward system, 30–45 min per session, once every 2 weeks. (4) Cognitive function: computer-assisted cognitive training using the virtual supermarket training system, 30–45 min per session, twice per week. (5) Sensory function: ① Auditory training using cards, 30–45 min per session, once weekly; ② Visual training using a bouncy ball, 30–45 min per session, once weekly. (6) Health education and guidance: it was delivered through thematic education sessions, covering essential health topics, conducted once per week for 30–45 min. All intervention sessions will be conducted in the nursing home’s activity room to ensure accessibility and consistency for participants.

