##### Hearing test

2.6.1.6

The hearing test will be conducted using an automated application to ensure accuracy and reliability. The testing environment will require ambient noise to be <40 dB. The “Hearing Bao” APP will be used to test both the left and right ears, and ambient noise levels will be recorded. The test will include frequencies of 125 Hz, 250 Hz, 500 Hz, 1,000 Hz, 2000 Hz, 4,000 Hz, and 8,000 Hz. However, for analysis, only the data from the WHO-recommended frequencies of 500 Hz, 1,000 Hz, 2000 Hz, and 4,000 Hz will be used. According to the standards, if the hearing test result for any ear in these four frequencies is ≤35 dB, the hearing function for that ear will be considered normal. Hearing function will be considered normal only when the test results for both ears are normal across all four frequencies.

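### The acuity and hearing tests are defined only as all-or-nothing classifications, which are insensitive to change, and unaided acuity cannot register benefit from the visual aids in Table 1.

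*Protocol article*

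**What the plan says.** **Vision (2.6.1.5).** Distance: "The participant will be asked to remove their glasses and stand 3 meters away from the visual acuity chart". Near: "The participant will be asked to remove their glasses and stand 33 cm away from the near vision chart". The cut-offs apply to each reading: "If the unaided distance vision of one eye is below 4.5, it will be considered impaired" and "If the unaided near vision of one eye is below 1.0, it will be considered impaired". The readings are then combined: "If any of the distance or near vision results for the left, right, or both eyes show impairment", vision as a whole is abnormal.

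**Hearing (2.6.1.6).** An app tests each ear, and four frequencies (500, 1,000, 2,000 and 4,000 Hz) are kept for analysis, with a limit of 35 dB at each. The combined rule is: "Hearing function will be considered normal only when the test results for both ears are normal across all four frequencies". The section does not say whether hearing aids are worn.

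**Sensory component of the programme.** Table 1, domain 5, lists hearing devices, caregiver communication, magnifiers, lighting, glare reduction, obstacle removal and contrast. It says that "hearing aids do not cure or reverse hearing loss, but rather help improve auditory perception". Section 2.5.3.1 refers to Table 1 but then gives the sensory sessions as weekly card-based auditory training and "Visual training using a bouncy ball, 30–45 min per session, once weekly". Neither activity appears in Table 1.

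**Other sensory measurement.** The ICOPE screen (2.6.1.1), repeated at T0, T1 and T2, has a vision item on everyday difficulty or past treatment for eye disease. Its hearing item is a whisper test or perceived hearing. Neither requires aids to be removed.

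**The concern.** Sensory function is one of the domains the trial hopes to improve (Introduction, Intervention group and Conclusion sections). Three features weaken what the two dedicated sensory tests can show.

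1. The MMSE, SPPB and MNA each have a total score with a cut-off attached. For acuity and hearing, the cut-off classification is the only variable defined, and one failing reading decides it. A participant who improves on several readings but still fails one is recorded as unchanged.
2. Acuity is read without correction, while the visual part of Table 1 works through aids and surroundings. A gain from those cannot appear on the chart.
3. The two descriptions of the sensory component differ, so a reader cannot tell what a sensory result, positive or null, is evidence about.

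At stake is a null sensory result that cannot be interpreted, although the graded readings needed for a more sensitive analysis are taken in any case.

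**Working it through.** **Inputs from the protocol.** 35 per group before attrition and 42 after it (section 2.2); two-sided 0.05; vision readings (left, right, both) × (distance, near) = 6; hearing readings 2 ears × 4 frequencies = 8.

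**Assumptions, because the protocol gives no prevalence or SD.** The true shift is 0.5 SD on a normally distributed reading. The share of controls classed abnormal ranges from 50% to 95%. For the composite rules, each reading fails with probability 0.3, independently of the others.

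**Step 1: the plan's own figure.** For the within-between interaction, λ = f²·N·m/(1 − r) = 0.25² × 70 × 3/1 = 13.1, with 2 and 2 × (70 − 2) = 136 degrees of freedom. Power is 0.904 at N = 70 and 0.895 at N = 68, so the stated 70 (35 per group) reproduces. It is used here only as the arm size.

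**Step 2: continuous comparison at one visit.** Power = Φ(d·√(n/2) − 1.96) = Φ(0.5 × √17.5 − 1.96) = Φ(0.13) = 0.55.

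**Step 3: the same shift after dichotomising.** If a proportion p of controls is abnormal, the intervention proportion is Φ(Φ⁻¹(p) − 0.5). Power = Φ{(Δ − 1.96·SE₀)/SE₁}, where Δ is the difference in proportions, SE₀ the pooled and SE₁ the unpooled standard error. For p = 0.50: the intervention proportion is 0.309, Δ = 0.191, SE₀ = 0.117 and SE₁ = 0.115, which gives 0.37.

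| Controls abnormal | Intervention abnormal | Power, 35 per arm |
|---|---|---|
| 50% | 30.9% | 0.37 |
| 70% | 51.0% | 0.37 |
| 80% | 63.4% | 0.34 |
| 90% | 78.3% | 0.27 |
| 95% | 87.4% | 0.20 |
| Not dichotomised | – | 0.55 |

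**Step 4: the fall in abnormality needed for 80% power.** With 35 per arm, and control prevalence from 50% to 95%, it is about 25 to 33 percentage points. With 42 per arm it is 22 to 30 points.

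**Step 5: how the composite rules respond.** P(abnormal) = 1 − 0.7^k. For vision, 1 − 0.7⁶ = 0.88; for hearing, 1 − 0.7⁸ = 0.94. Correcting one reading in every participant gives 1 − 0.7⁵ = 0.83 and 1 − 0.7⁷ = 0.92. A universal improvement in one reading therefore moves the outcome by about 5 and 2 points. Readings within a person are correlated, which lowers the prevalence of abnormality, so these figures mark the independence extreme.

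**Step 6: measure against content.** Magnifiers, lighting and contrast change what a person can do in their surroundings. They do not change what the uncorrected eye reads on a standard chart. Training sessions could in principle change an unaided reading. Whether the acuity test suits the component therefore depends on which of the two descriptions applies.

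**The case against.** A reader might infer that the programme's aids cannot show an effect on any sensory outcome. The documents do not support that. The ICOPE vision and hearing items are repeated at all three visits without removing aids, and they feed the intrinsic capacity score. They are a partial safeguard only: the vision item stays positive after any treatment for eye disease, and vision and hearing share one 0/1 domain in the 0–5 score.

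A reader might also infer that the graded readings will be discarded, or that hearing is tested without aids. Neither is stated. Section 2.8 has methods for continuous variables, and the choice of modelled form may sit in an analysis plan that is not shown. Even so, the article defines no graded variable for these two tests, in contrast to the other scales.

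The abnormality rates are assumptions, and the protocol excludes severe sensory impairment that prevents clear communication. Near-constant outcomes are therefore not established. The calculation shows reduced power, not none.

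Finally, the Introduction separates intrinsic capacity (the person's own abilities) from functional ability (those abilities in an environment). Unaided acuity is arguably the right measure of the former, so an aided reading cannot be called a requirement. That part of the objection stands. It does not rescue the all-or-nothing rules or resolve the two descriptions of the component.

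**Conclusion.** The point holds in a limited form. As defined, the acuity and hearing variables are insensitive to change. Under an assumed 0.5 SD shift with 35 per arm, power falls from about 0.55 to between 0.37 and 0.20 as the share of controls classed abnormal rises from 50% to 95%. Power is lower than the continuous analysis at every prevalence tried, but the exact loss depends on these assumptions.

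The unaided acuity result cannot speak to the visual aids and adaptations in Table 1. For hearing, the defect is narrower: device status at testing is unstated, so a change in status between visits could be mistaken for a change in hearing. The conflict between Table 1 and section 2.5.3.1 rests on the text alone and needs no assumption.

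The primary outcome is overall intrinsic capacity, so this limits the sensory claim and does not invalidate the trial.

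**What to change.** 1. Name graded distance acuity, graded near acuity and the average threshold over 500, 1,000, 2,000 and 4,000 Hz in dB as continuous outcomes in the planned mixed model. State in advance which eye and ear are used (for example the better one). Keep normal/abnormal as descriptive. This uses readings already taken and costs only a few lines of text.
2. State whether hearing aids are worn at testing, hold that the same at every visit for each participant, and record it. This costs one field on the form.
3. Reconcile the sensory component in Table 1 with that in section 2.5.3.1, so that it is clear what is delivered.
4. State that the unaided acuity result will not be interpreted as evidence about the visual aids and adaptations.
5. Optional: one further reading with the participant's usual glasses or device. It adds visit time, its feasibility with the hearing app is not shown, and a chart reading would still miss changes to the participant's surroundings.

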### Eligibility and recruitment

2.3

Participants will be recruited from nursing home in Changchun, Jilin Province, China. The old patients with disabilities in nursing homes will be recruited through live lecture, poster promotion and official account by researchers and staff. Eligible subjects will be screened through face-to-face surveys. Inclusion criteria for participants will be: (1) Will be aged ≥60 years; (2) Will reside in a nursing home; (3) Will be classified as having mild to moderate disability according to the Ministry of Civil Affairs’ National Standard for Elderly Ability Assessment; (4) Will volunteer to participate in the study and sign informed consent. Participants will be excluded if: (1) Older adults with severe cognitive impairment or severe mental disorders who are unable to comply with the study procedures; (2) Older adults with severe hearing or visual impairments that prevent clear and fluent communication.

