##### ICOPE intrinsic capacity screening tool

2.6.1.1

The assessment of intrinsic capacity strictly follows the five domains proposed by the WHO (33): cognition function, motor function, sensory function (Vision and Hearing), vitality, and psychological function. Each domain is scored as 0 (normal) or 1 (impaired), and the total intrinsic capacity score is the sum of the five domain scores, ranging from 0 to 5. A score of 3 to 5 is defined as low intrinsic capacity, while a score of 0 to 2 is classified as high intrinsic capacity. Specific contents include: ① Cognitive function: Screening assesses memory and temporal orientation, including word recall (flower, door, rice), time and place orientation, and short-term memory tests. An incorrect response or failure to recall all three words indicates a positive screening result. ② Motor ability: The chair rise test is used to assess mobility. Participants must stand up and sit down five times consecutively without using their arms for support, completing the task within 14 s. Failure to meet this requirement is considered a positive screening result. ③ Nutrition: Assesses weight changes and dietary habits over the past 3 months, including whether the individual has experienced weight loss of ≥3 kg or frequently finds food tasteless or difficult to swallow. A “yes” to either question indicates a positive screening result. ④ Vision: Assess whether there are visual difficulties (e.g., watching TV, reading, or recognizing faces) or a history of eye disease treatment. A positive response to either indicates a positive screening result. ⑤ Hearing: Use the whisper test or inquire about subjective hearing perception. Failure in the test or a significant perceived decline in hearing is considered a positive screening result. ⑥ Depression: Assess recent emotional state, including feelings of low mood, depression, or hopelessness, or loss of interest in daily activities. The presence of these symptoms indicates a positive screening result.

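### Vision class joins a distance cut-off of 4.5 and a near cut-off of 1.0 without notation, so near vision may set the result alone and hide change in distance vision

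*Protocol article*

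**What the plan says.** Section 2.6.1.5 (Visual acuity test) of the protocol article describes two tests, both with glasses removed, each for the left eye, the right eye and both eyes. The distance test is read at 3 metres: "If the unaided distance vision of one eye is below 4.5, it will be considered impaired". The near test uses its own chart, for which the participant will "stand 33 cm away from the near vision chart". Its limit is: "If the unaided near vision of one eye is below 1.0, it will be considered impaired". The notation of neither chart is named.

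The two tests are then merged into one class: "If any of the distance or near vision results for the left, right, or both eyes show impairment, the participant’s vision will be considered abnormal". This normal/abnormal class is the only vision result that the section defines. Table 2 schedules the test at T0, T1 and T2.

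Section 2.3 recruits people by the criterion "Will be aged ≥60 years" and excludes "Older adults with severe hearing or visual impairments that prevent clear and fluent communication".

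**The concern.** The two limits can hardly be values on one scale, and the any-failure rule makes the stricter test dominant. The stricter test might be near vision, by a wide margin. In that case the class would mostly record whether a resident aged 60 or over can meet a fine standard at 33 cm without glasses, and change in distance vision would barely register. A finding of no effect on vision could then come from the scoring rule, and the baseline share with abnormal vision would depend mainly on one unexplained number. The programme includes weekly visual training (section 2.5.3.1), so the vision result will be read as evidence about that component.

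**Working it through.** **Inputs from the protocol.** Limits of 4.5 (distance) and 1.0 (near), near distance 33 cm, glasses off, any failed reading counts as abnormal, age 60 or over. Sample size from section 2.2: 35 per group needed, 42 per group enrolled.

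**The plan's own figure.** Section 2.2 gives 70 participants for the within-between interaction (f = 0.25, alpha 0.05, power 0.90, three measures, correlation 0). With noncentrality f² × N × 3 = 0.0625 × 70 × 3 = 13.1 and 2 and 136 degrees of freedom, power is 0.904; at N = 69 it is 0.8999. So 70 reproduces. It does not concern the vision class and is used here only for the group size of 35.

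**Assumptions not in the protocol.** Five-grade value = 5 + log10(decimal acuity). The protocol gives no failure rates, so they are varied below.

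**Step 1: what the limits mean.**
- Distance 4.5 as five-grade: 10^(4.5 − 5) = 0.316 decimal.
- Reading (a), near 1.0 as decimal: 5 + log10(1.0) = 5.0 five-grade. The near limit is 0.5 log unit stricter; 1.0/0.316 = 3.16 times. Reading at 33 cm needs 1/0.33 = 3.0 dioptres of focus.
- Reading (b), near 1.0 as five-grade: 10^(1 − 5) = 0.0001 decimal. Practically nobody who passes the communication exclusion would fall below it. The near test adds no cases, and the class equals the distance result.

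**Step 2: the combined class under (a).** Let q be the share failing near and d the share failing distance. If failures are independent, the abnormal share is 1 − (1 − q)(1 − d), so a change in d is multiplied by (1 − q). Take d = 40% in one arm and 20% in the other, and use the exact two-sided Fisher test with 35 per arm:

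| q (assumed) | Abnormal share, d = 40% | Abnormal share, d = 20% | Difference (points) | Power |
|---|---|---|---|---|
| 0 (distance alone) | 40% | 20% | 20 | 0.36 |
| 50% | 70% | 60% | 10 | 0.10 |
| 70% | 82% | 76% | 6 | 0.05 |
| 85% | 91% | 88% | 3 | 0.02 |
| 90% | 94% | 92% | 2 | 0.01 |
| 95% | 97% | 96% | 1 | 0.001 |
| 98% | 98.8% | 98.4% | 0.4 | <0.001 |

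With 42 per arm, power is 0.44 for distance alone and 0.03 at q = 85%. If everyone who fails distance also fails near, the abnormal share is the larger of q and d. For q of 40% or more, both arms then show q, and the distance change disappears completely.

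**Step 3: is it simply a ceiling problem?** No. At 35 per arm, a 10-point difference has power 0.136 at 95% v 85% and 0.097 at 40% v 30%. A given difference in the class is no harder to detect near the ceiling. The loss arises because a real change in distance vision produces only a small difference in the class.

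**The case against.** The strongest reply has five parts.

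- **Different notations are not an error.** Two tests on two charts may use two scales, and a condensed article may leave chart details to the full protocol. This stands. What remains is that the article fixes two limits and one combining rule, and their relative strictness cannot be determined from the text.
- **The failure rates are assumed.** This stands too. The 85-98% range is not from the protocol, so the table also shows lower rates. Masking is milder there, but at 50% power has already fallen from 0.36 to 0.10.
- **The high near-failure rate depends partly on removing glasses.** Correct. With near correction worn, the argument for a very high rate would weaken. The difference in strictness under reading (a) would remain.
- **Acuity may be analysed as a value.** Section 2.8 provides for continuous and categorical variables and does not restrict vision to the class. But section 2.6.1.5 defines only the class, so the point needs stating.
- **The reach is small.** The vision item of the ICOPE screening tool is separate: "Assess whether there are visual difficulties (e.g., watching TV, reading, or recognizing faces) or a history of eye disease treatment". It does not use these limits, so the screening score is untouched.

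A reader might infer that nearly everyone or no one fails the near test, and that vision therefore cannot separate the arms. The documents do not support that. They give no failure rates. Under reading (b) the class still reflects distance vision and can differ between arms. Under reading (a) a large difference in the class remains detectable: 95% v 75% has power 0.55 at 35 per arm.

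**Conclusion.** The point holds in limited form. The plan combines two limits of unnamed notation into one any-failure class. If 4.5 is five-grade and 1.0 is decimal, the near limit is about 3.2 times stricter. Near vision could then largely determine the class, and change in distance vision would be masked: power falls from 0.36 to about 0.02 or less for a 40% to 20% improvement when 85-98% fail near. If both numbers are five-grade, near vision is in effect not tested. These sizes rest on the assumed notation, the assumed failure rates and independence of near and distance failure. The consequence is confined to the acuity outcome. It deserves correction because it costs little, but it does not threaten the trial's main conclusion on the ICOPE screening score.

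**What to change.** 1. Analyse and report distance and near vision separately at T0, T1 and T2, preferably as the recorded acuity values, so that the near criterion alone cannot set the vision result.
2. Name the notation of each chart.
3. Express both limits on one stated scale, and reconcile or justify their different strictness.
4. If the combined class is kept, present it as a secondary description beside the two separate results.

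The cost is wording and analysis only. Both readings are already planned at every visit, and recorded values can be re-scored. The downside is that results on the combined class become less comparable with other work that uses it.
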